# ===== Test Data Generation =====
if __name__ == '__main__':
    np.random.seed(42)
    n_train = 30
    n_test = 20
    train_events = np.random.choice([True, False], size=n_train, p=[0.7, 0.3])
    train_times = np.random.uniform(1, 20, size=n_train)
    survival_train = np.array(list(zip(train_events, train_times)),
                              dtype=[('event', 'bool'), ('time', 'float')])
    test_events = np.random.choice([True, False], size=n_test, p=[0.5, 0.5])

```

```

test_times = np.random.uniform(1, 20, size=n_test)
survival_test = np.array(list(zip(test_events, test_times)),
                          dtype=[('event', 'bool'), ('time', 'float')])

n_times = 5
estimate = np.random.rand(n_test, n_times)
times = np.linspace(1, 20, n_times)
res, res_mean = cum_metrics(survival_train, survival_test, estimate, times,
AUC_sfd=False)
print("Detailed metrics for each time point:")
for key, value in res.items():
    print(f"{key}: {value}")

if res_mean:
    print("\nMean metrics (integrated over time):")
    for key, value in res_mean.items():
        print(f"{key}: {value}")

```

## 8 Sample Size and Power

For sample size calculation, we employed two approaches. The first approach involves screening the proteins, while the second focuses on constructing a predictive model. Both approaches are based on the Cox proportional hazards (Cox PH) model.

### 8.1 Sample size for screening the proteins

Sample size estimation for screening the proteins base the Cox proportional hazards model was performed using the Schoenfeld formula. The required number of events  $D$  is given by:

$$D = \frac{(z_{1-\alpha/2} + z_{1-\beta})^2}{p(1-p)[\ln(HR)]^2},$$

where:

- $\alpha$  is the two-sided significance level (set to 0.05, so that  $z_{1-\alpha/2} \approx 1.96$  ).
- $\beta$  is the Type II error rate (with statistical power =  $1 - \beta$ ).
- $p$  is the expected proportion of subjects who with marker-positive (in this study, 30% or  $p = 0.3$ ).
- $\ln(HR)$  is the natural logarithm of the hazard ratio to be detected.

The total sample size  $N$  is then calculated by adjusting the required number of events by the expected event rate during follow-up:  $N = \frac{D}{\text{event rate}}$

In our study, we assumed:

- an expected event rate of 25% (i.e., 0.25),
- an anticipated hazard ratio of approximately 1.648 (which is close to  $\exp(0.5)$ ).

Under these assumptions, enrolling 685 subjects would yield an effective statistical power of about 85% for detecting a hazard ratio of 1.648 (Figure 1). The pseudo code is as follows:

```

import math
import numpy as np
import matplotlib.pyplot as plt
from scipy.stats import norm
import pandas as pd
def calculate_sample_size_cox(alpha, power, hr, p=0.5, event_rate=1.0):
    """
    Calculate the required sample size for a Cox proportional hazards model
    based on the Schoenfeld formula.
    Parameters:
        alpha (float): Significance level (Type I error rate), e.g., 0.05.
        power (float): Statistical power (1 - beta), e.g., 0.8.
        hr (float): Hazard ratio to detect, e.g., 1.65.
        p (float): Proportion of subjects in the designated group (default is 0.5).
        event_rate (float): Expected event rate during the study period (default is 1.0, meaning
all subjects experience the event).
    Returns:
        n (int): Estimated total sample size required.
    """

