#### 3.2 Penn Medicine BioBank (Primary Cohort)

PMBB is an EHR-linked biobank at the University of Pennsylvania with >40,000 participants, ~30% non-European ancestry. We will identify all African-American PMBB participants with APOL1 high-risk genotype (two risk alleles: G1/G1, G2/G2, or G1/G2), age ≥18, and baseline eGFR >60 mL/min/1.73m^2. APOL1 genotype was determined via whole-exome sequencing (Regeneron) or equivalent genotyping. Plasma proteomic profiles (7,549 proteins) were measured at baseline using the SomaScan aptamer platform. We have identified 1,113 eligible participants for the primary cohort (expanded from 550 in the prior dataset). Additional CKD participants with APOL1 high-risk genotype and 967 African ancestry APOL1 low-risk participants (267 newly added) and 698 European ancestry APOL1 low-risk were included as external reference. Baseline covariates include age, sex, eGFR (CKD-EPI 2021), and albumin-to-creatinine ratio (UACR). To better enable comparison between the African ancestry APOL1 high-risk and low-risk groups, propensity score matching was applied using age, sex, eGFR, UACR, diabetes, hypertension, and cardiovascular disease, with separate matching performed for participants with eGFR >60 and ≤60 mL/min/1.73 m^2 (Appendix 1 to 3).

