## **3 Cohorts, inclusion criteria, and analytic sets**

Primary derivation set (APOL1-HR, preserved eGFR):

Inclusion: APOL1 genotype = high-risk (two risk alleles: G1/G1, G2/G2, G1/G2), available plasma proteomics (SomaScan platform), baseline eGFR > 60 mL/min/1.73 m^2 measured at or 2 months before or 1 month after of sampling, available UACR (or imputed as specified).

Final sample size in derivation set:  $N = 851$ . Baseline descriptive statistics, event counts, and follow-up summaries are provided in manuscript. Key cohort summary (derivation APOL1-HR preserved-eGFR): mean age 49.2 years; female proportion 66.5%; mean eGFR 90.6 mL/min/1.73 m^2; median UACR 17.23 mg/g; composite event rate 17.98% ( $n = 153$ ); mean time to event 6.51 years; median follow-up 7.3 years.

Secondary analytic sets:

APOL1-HR with existing CKD at baseline: 262 participants included for comparison and benchmarking of APRS behavior in established disease.

APOL1-low-risk extension: an additional 995 participants to evaluate specificity and cross-genotype performance.

EUR comparison set (review-only):  $N = 514$  (used for method comparisons but not central to the APOL1-focused primary aims).

External validation cohorts

ARIC (Atherosclerosis Risk in Communities): African-ancestry subset with SomaScan proteomics (where available).

UK Biobank (UKB): African-ancestry subset with Olink proteomics (smaller targeted panels). Because platforms differ, apply the prespecified cross-platform mapping and multi-output imputation.

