### 6.2 Statistical Analysis for Multiplicity Correction

We will address multiple hypothesis testing by applying Benjamini-Hochberg false discovery rate (FDR) correction to all univariate analyses of proteomic biomarkers, ensuring that the overall rate of false positives remains controlled. Specifically, we will first calculate raw p-values from Cox proportional hazards models (or comparable methods) for each protein, then adjust these p-values using FDR at a predefined threshold (e.g., FDR < 0.05). In cases where a more stringent control of type I error is required—such as validating a smaller panel of

high-priority protein biomarkers—we will consider Bonferroni or Holm-Bonferroni methods. All statistical analyses will be performed using Python (including the `statsmodels.stats.multitest` module) and R (e.g., the `p.adjust` function) to maintain reproducibility. Finally, we will report effect estimates (with 95% confidence intervals) for each protein and appropriately highlight any exploratory findings that do not undergo formal multiplicity adjustment.

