### EPV-Based Sample Size Calculation

In parallel, we applied the widely used rule-of-thumb based on the events per variable (EPV) criterion. According to this approach, a minimum number of events per predictor is required to reliably estimate model parameters. The required number of events  $D$  is given by:

$$D = EPV \times k$$

where EPV is typically set to 10 (or adjusted to 11 or 12 in sensitivity analyses) and  $k$  represents the number of candidate predictors. Given an expected event rate (denoted as  $\lambda$ ), the total required sample size  $N$  is then calculated as:

$$N = \frac{D}{\lambda} = \frac{(EPV \times k)}{\lambda}$$

For example, assuming an event rate of 25%, the total sample size for an EPV of 10 would be computed as:

$$N = \frac{10 \times k}{0.25}$$

This calculation was performed across a range of  $k$  values, and similar computations were repeated for EPV values of 11 and 12 to assess the sensitivity of the sample size requirement (Figure 2).

In our study, we assumed:

- an expected event rate of 25% (i.e., 0.25),
- candidate predictor numbers ranging up to 15, and
- performance parameters as specified by the global  $R^2$ , where  $R_{app}$  equal to 0.88

The required total sample sizes were:

- EPV = 10: sample size = 640,
- EPV = 11: sample size = 704,
- EPV = 12: sample size = 768.
- Riley's method sample size = 782

Based on these estimates, we ultimately adopted a sample size of 700 participants. This choice is consistent with our initial sample size estimation for protein screening and is expected to provide sufficient power for robust predictive modeling while minimizing the risk of overfitting. The pseudo code is as follows:

```

import math
import numpy as np
import pandas as pd
import matplotlib.pyplot as plt
#####

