### Sample Size Estimation Using Riley's Method and the EPV Rule.

The figure illustrates the required total sample size for predictive modeling as a function of the number of candidate predictors ( $k$ ), estimated using both Riley's method (solid red line) and the EPV rule with different assumptions ( $EPV = 10, 11$ , and  $12$ , represented by solid black, blue, and green lines, respectively). Riley's method accounts for model performance characteristics and expected shrinkage, while the EPV rule provides a heuristic estimation based on the number of events per variable. The dashed red horizontal line indicates a reference sample size of 700 participants, and the dashed blue vertical line corresponds to a scenario with 17 candidate predictors. These reference lines aid in visualizing feasible study designs under different methodological assumptions.

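### SAP section 8 assumes a 25% event rate that the derivation set did not reach and mixes three predictor counts, so its power and overfitting statements need restating

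*Combined protocol and SAP*

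**What the plan says.** SAP 8.1 applies the Schoenfeld formula with two-sided alpha 0.05, a marker-positive proportion of 30%, a 25% event rate and a hazard ratio of 1.648. It concludes that "enrolling 685 subjects would yield an effective statistical power of about 85% for detecting a hazard ratio of 1.648".

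SAP section 3 describes the derivation set as 851 people with "composite event rate 17.98" per cent (153 events). Supplementary Table 1 gives 121 events among the 680 training participants. Protocol 3.7 selects proteins in the training set, and SAP 6.4.3 takes the final coefficients from it. SAP 6.2 plans "applying Benjamini-Hochberg false discovery rate (FDR) correction to all univariate analyses of proteomic biomarkers".

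SAP 8.2 assumes "candidate predictor numbers ranging up to 15" and lists four requirements: "EPV = 10: sample size = 640", then 704 and 768 for EPV 11 and 12, and 782 by Riley's method. It continues: "Based on these estimates, we ultimately adopted a sample size of 700 participants", and says that this size should keep the risk of overfitting small. The plotting code marks 15 predictors, but the legend says that its reference line "corresponds to a scenario with 17 candidate predictors". The text of 8.2 gives the event rate as 25%, while the printed Riley code enters 0.24.

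Protocol 3.2, after setting an eGFR criterion above 60, says: "We have identified 1,113 eligible participants for the primary cohort".

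**The concern.** Section 8 tells the reader that the study has enough events to screen proteins and to fit a stable model. Both statements are written as if the 25% event rate held, yet the same SAP reports 17.98% and does not reconcile the two. The predictor count behind the EPV sizes is neither of the two counts given, and the printed Riley code does not carry the event rate stated in the text. A reader who takes the section at face value would credit the screen with more power, and the coefficients with more protection against overfitting, than the events provide.

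**Working it through.** **Power (SAP 8.1).** Inputs from 8.1: z = 1.960 for alpha, z = 1.036 for 85% power, ln(1.648) = 0.4996, and p(1−p) = 0.3 × 0.7 = 0.21.

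The plan's own figure: D = (1.960 + 1.036)² / (0.21 × 0.4996²) = 171.3 events, and 171.3 / 0.25 = 685.3 people. The stated 685 and 85% reproduce.

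With other event counts, power = Φ(√(0.21 × D) × 0.4996 − 1.960):

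| Set | Events D | Argument of Φ | Power |
|---|---|---|---|
| 685 people at 25% | 171.25 | 1.036 | 85.0% |
| 685 people at 17.98% | 123.2 | 0.581 | 71.9% |
| Derivation set, 851 | 153 | 0.872 | 80.8% |
| Training set, 680 | 121 | 0.558 | 71.2% |

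At 17.98%, 85% power would need 171.3 / 0.1798 = 953 people. Equivalently, the hazard ratio detectable with 85% power is exp(2.996 / √(0.21 × 153)) = 1.70 in the full set and exp(2.996 / √(0.21 × 121)) = 1.81 in the training set.

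**EPV sizes (SAP 8.2).** N = EPV × k / 0.25:

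| k | EPV 10 | EPV 11 | EPV 12 |
|---|---|---|---|
| 15 (text, code) | 600 | 660 | 720 |
| 16 | 640 | 704 | 768 |
| 17 (legend) | 680 | 748 | 816 |

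The printed sizes are exactly those for k = 16.

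**Riley figure (SAP 8.2).** R² = (0.88 − 0.5)² / 0.75 = 0.1925. Two criteria were coded from their formulas, and the larger N applies. The R package itself was not run, and any further criterion it uses is not covered.

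- Shrinkage 0.9: N = k / ((0.9 − 1) × ln(1 − R²/0.9)), which is 624 at k = 15 whatever the rate.
- R² optimism 0.05: N = k / ((S − 1) × ln(1 − R²/S)), with S = R² / (R² + 0.05 × maxR²), maxR² = 1 − exp(2(m ln m − m)), and m = rate × mean follow-up, the events per person.

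| Rate (k = 15, follow-up 10) | m | maxR² | S | Optimism N | Larger N |
|---|---|---|---|---|---|
| 0.25 (text) | 2.5 | 0.342 | 0.918 | 782 | 782 |
| 0.24 (code) | 2.4 | 0.450 | 0.895 | 593 | 624 |
| 0.025 (25% over 10 years, per year) | 0.25 | 0.697 | 0.847 | 380 | 624 |

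So 782 arises at k = 15 and rate 0.25. Read as a yearly rate with 10 years of follow-up, that is 2.5 events per person, which contradicts a 25% event rate.

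**Achieved events per variable.** Full set: 153/15 = 10.2 and 153/16 = 9.6. Training set: 121/15 = 8.1 and 121/16 = 7.6. For the final model of nine proteins and four covariates, 121/13 = 9.3. SAP 6.4.2 searches the top 20% of proteins; with the 7,549 in protocol 3.2 that is about 1,510 candidates, and 121/1,510 = 0.08 events per candidate.

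**Cohort count (protocol 3.2).** Appendix 1 has 851 high-risk people with eGFR above 60, and Appendix 2 has 262 at or below 60. 851 + 262 = 1,113, the all-eGFR total in Appendix 3.

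**The case against.** The strongest reply is that 8.1 is a planning calculation stated under explicit assumptions, and that it is arithmetically right. That stands: a reader might infer a calculation error, and there is none. Putting achieved events into a planning formula is also a post-hoc exercise, and in the full derivation set the loss is only from 85% to 81%. The whole high-risk group did have 298/1,113 = 26.8% events, but SAP section 3 defines the derivation set as the 851.

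Three stronger readings are tempting and not supported.

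- That 700 fails most of its own requirements. It is below 704, 768 and 782, but EPV 11 and 12 are labelled as sensitivity values, 700 meets the base EPV 10 size, and at k = 15 the EPV 11 size falls to 660. The achieved 851 exceeds all four printed sizes.
- That 782 cannot be reproduced. This would follow only from checking the shrinkage criterion alone, which gives 748 at k = 18 and 790 at k = 19.
- That power for the screen collapses under Bonferroni. SAP 6.2 plans false discovery rate control and only considers stricter methods for a smaller panel. The threshold that this control would imply cannot be derived from the documents. Model candidates are also ranked by univariate AUC (SAP 6.4.2), so this power does not decide which proteins enter the score.

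It is also fair that 9.3 events per fitted variable is only just below a rule of thumb, and that the fit is penalised. But 8.2 counts candidate predictors, and neither 15 nor 16 describes a search over about 1,510 proteins.

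**Conclusion.** The point holds as an unmet planning assumption together with inconsistent inputs. The 85% in 8.1 is right at a 25% event rate. With the events reported it is about 81% in the derivation set and about 71% in the training set, for HR 1.648, 30% marker-positive and one two-sided test at 0.05. Under the planned false discovery rate control both are upper readings, by an amount that the documents do not fix.

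In 8.2 the EPV sizes use a predictor count that appears nowhere in the text, code or legend. The Riley figure uses a rate different from the printed code, and apparently on the wrong time scale. The Riley conclusion rests on the two criteria coded here and on reading the rate as per year. If 624 is the correct figure, 700 would meet it. As printed, 700 is below 782 and the SAP does not say why that is acceptable.

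The shortfall is in events rather than people. At 8.1 training events per predictor for k = 15, and 0.08 per candidate protein, the statement that overfitting risk is kept small has no support in section 8. This does not show that the score is overfitted, only that the sample size section cannot be cited as evidence against it.

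**What to change.** - In SAP 8.1, keep the planning figure but add the achieved events and power: 153 events, about 81%; 121 training events, about 71%. Say that these are for a single test at 0.05, before false discovery rate control.
- In SAP 8.2, use one predictor count in text, code and legend, and correct the EPV sizes (600, 660 and 720 if it is 15).
- Re-run Riley's method with one stated rate, on a stated time scale, the same in text and code, and explain how the adopted 700 relates to the result.
- Replace the overfitting statement with the achieved events per variable and per candidate, and an estimated shrinkage factor or calibration slope.
- In protocol 3.2, change 1,113 to 851 for the primary cohort.

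The cost is wording, one re-run of the sample size code and one shrinkage estimate. The stated figures become less favourable; no more participants are needed.

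### The 85% power given in SAP 8.1 for protein screening is power for one unadjusted test at 0.05, not for the FDR-controlled protein tests planned in SAP 6.2

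*Combined protocol and SAP*

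**What the plan says.** SAP section 8.1 sizes the protein screen with the Schoenfeld formula for one binary marker. Its alpha "is the two-sided significance level (set to 0.05, so that" the normal quantile is about 1.96. On its stated inputs it concludes that "enrolling 685 subjects would yield an effective statistical power of about 85% for detecting a hazard ratio of 1.648". Neither the text nor the accompanying code contains a number of proteins or a multiplicity term.

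SAP section 6.2 sets a different decision rule for the protein tests. It commits to "applying Benjamini-Hochberg false discovery rate (FDR) correction to all univariate analyses of proteomic biomarkers", using a Cox p-value for each protein. FDR below 0.05 is given as an example threshold, and Bonferroni or Holm is held in reserve for a smaller priority panel of unstated size. On scale, Protocol section 3.2 says: "Plasma proteomic profiles (7,549 proteins) were measured at baseline".

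SAP section 8.2, after its EPV and Riley estimates, adopts 700 participants and adds: "This choice is consistent with our initial sample size estimation for protein screening and is expected to provide sufficient power". The sentence goes on to tie that power to predictive modelling.

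**The concern.** A power figure describes a particular test at a particular cut-off. The one in section 8.1 belongs to a test at p ≤ 0.05, whereas a protein is declared under section 6.2 only if it passes the Benjamini-Hochberg cut-off, which is stricter. The SAP describes no other per-protein significance test to which the 85% could apply.

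A reader of section 8.1 would therefore expect a protein with a true hazard ratio of 1.648 to be found about 85 times in 100, when the planned tests would find it less often. The mismatch does not depend on the event rate, since it is present at the plan's own 25%.

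**Working it through.** **Inputs**
- Hazard ratio: "an anticipated hazard ratio of approximately 1.648 (which is close to" exp(0.5)), SAP 8.1.
- Marker-positive proportion 0.3, SAP 8.1.
- Event rate: "an expected event rate of 25% (i.e., 0.25"), SAP 8.1.
- Two-sided alpha 0.05 for one test, SAP 8.1.
- FDR level q = 0.05, given as an example, SAP 6.2.
- Fraction of proteins declared, f: not in the documents. Assumed here at 50%, 10% and 1%.

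**Step 1: reproduce the plan's figure.** Events D = (z for alpha + z for power)² / [p(1−p)(ln HR)²] = (1.960 + 1.036)² / [0.21 × (ln 1.648)²] = 171.3. Dividing by 0.25 gives 685.3. Using exp(0.5) instead of 1.648 gives D = 171.02 and, rounded up, exactly 685. In the other direction, 685 × 0.25 = 171.25 events. The noncentrality is √(171.25 × 0.21) × ln 1.648 = 2.996, and power = Φ(2.996 − 1.960) = 0.850. The stated figure is right for one two-sided test at 0.05. A one-sided 0.05 test would give 0.912, so that is not what was used.

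**Step 2: find the cut-off that section 6.2 implies.** If Benjamini-Hochberg declares k of m proteins, the largest p-value that can be declared is q × k/m = 0.05 × f. This equals 0.05 only when f = 1. For a given f it does not depend on m, so it does not matter that the number of proteins tested after quality control is unstated.

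**Step 3: recompute at that cut-off**, keeping 171.25 events. Power = Φ(2.996 − z). Detectable HR at 85% power = exp[(z + 1.036) / √(171.25 × 0.21)], where the square root is 5.997.

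| Fraction declared (assumed) | Cut-off | z | Power at HR 1.648 | HR detectable at 85% |
|---|---|---|---|---|
| 100% (same as one unadjusted test) | 0.05 | 1.960 | 85.0% | 1.648 |
| 50% | 0.025 | 2.241 | 77.5% | 1.73 |
| 10% | 0.005 | 2.807 | 57.5% | 1.90 |
| 1% | 0.0005 | 3.481 | 31% | 2.12 |

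Power falls to 80% at a cut-off of 0.031, that is, when about 62% of proteins are declared.

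**Step 4: cross-check from the other side.** Instead of fixing the fraction declared, assume a share of proteins truly associated at HR 1.648 and solve for the cut-off. With 7,549 independent tests, average power is about 19% if 1% are associated, 49% if 10%, 60% if 20% and 74% if 50%. If all are associated it is 83%. Simulation of independent tests (1,000 runs per setting) agreed at the shares of 50% and below. The shares and the independence are assumptions, but no share brings power to 85%.

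**The case against.** The best reply is that section 8.1 hides nothing. It lists its alpha, hazard ratio, marker proportion and event rate, and its figure follows from them. That is correct: there is no arithmetic error. The fault is that the result is presented as the sample size for screening without saying that it covers one marker at an unadjusted level. The general statement in Protocol section 3.7 that tests use alpha 0.05 does not help, because SAP section 6.2 specifically governs the protein tests.

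It is also true that FDR 0.05 is only an example and that the fraction declared is unknown. Both affect the size of the loss. At FDR 0.05, neither affects its direction.

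Several stronger readings are tempting, and the documents do not support them:
- *A reader might infer that APRS protein selection is underpowered.* SAP section 6.4.2 draws candidates from the top fifth by univariate AUC and then fits penalised Cox models. FDR significance is nowhere a condition of entry.
- *A reader might infer that 700 participants rests on the screening power.* SAP section 8.2 says only that 700 agrees with the screening estimate. Its adequacy claim concerns the prediction model and follows the EPV and Riley figures.
- *A reader might infer that non-significant proteins will be treated as ruled out.* No section plans this, and section 6.2 promises estimates with 95% confidence intervals for every protein.
- *A reader might quote power under Bonferroni over all 7,549 proteins, or over a nine-protein panel.* The first is not a planned rule. For the second, nine is the size of the final score, while section 6.2 gives no panel size.

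**Conclusion.** The point stands in this form: the 85% in SAP section 8.1 is single-marker power and overstates the power of the FDR-controlled univariate tests in section 6.2. At FDR 0.05 and the plan's own 171 events, the shortfall is about 7.5 percentage points if half the proteins are declared (85.0 − 77.5), 27.5 points if a tenth are (85.0 − 57.5), and 54 points if one in a hundred are (85 − 31). That the power is lower follows from the Benjamini-Hochberg rule itself, unless every protein is declared. How much lower depends on the fraction declared, which is assumed here.

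The consequence is limited to how the univariate protein results are described and read. It does not reach the AUC-rank and elastic-net construction of the APRS.

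**What to change.** In SAP section 8.1, state that 685 participants and 85% power apply to one prespecified protein tested at two-sided 0.05. Beside it, give the power at HR 1.648, or the hazard ratio detectable with 85% power, at the FDR level used in section 6.2, over a stated range of assumed fractions declared. On the range used here the entries would be 77.5%, 57.5% and 31%, or hazard ratios of 1.73, 1.90 and 2.12, for 50%, 10% and 1% declared.

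The existing sample-size function can be rerun with alpha set to 0.05 times the assumed fraction. Its hazard-ratio grid stops at 2.0 and must be extended to cover the 1% case.

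In SAP section 8.2, qualify the reference to the protein-screening estimate by saying that it is single-marker power without multiplicity adjustment.

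The cost is a few sentences and a rerun of existing code. No additional participants or data are needed. The only downside is a less favourable stated figure.
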